**APPENDIX 2**

**Maltodextrin 10 g single-dose product characteristics**

**Xalabarder Pharmacy ([name])**

1. **PRODUCT DESCRIPTION**

Maltodextrin 10g single-dose.

1. **COMPOSITION**

This product consists of 10g of maltodextrin per unit.

1. **PRESENTATION**

Single-dose sachets with 10g of product.

Boxes of 60 sachets.

6 boxes for each treatment.

1. **RAW MATERIAL**

Raw material purchased from Fagron Ibèrica.

The certificate of analysis lists the following assays and results:

|  | **MALTODEXTRIN** | |
| --- | --- | --- |
| **ASSAYS** | | RESULTS |
| **Identification** | | Passed |
| **Loss through desiccation** | | 4.74% |
| **Heavy metals** | | <10ppm |
| **Sulphur ash** | | <0.5% |
| **pH** | | 6.02 |
| **Sulphur dioxide** | | <5ppm |
| **Total airborne material** | | <10ufc/g |
| **Fungi and yeast** | | <10ufc/g |
| **E. Coli** | | Passed |
| **Salmonella** | | Passed |
| **Dextrose** | | Passed |
|  | | **SPECIFICATION COMPLEX** |

1. **PACKAGED MATERIAL**

Thermally sealed aluminum and cellulose Surling-type blister pack.

Sachets are marked with production reference number and expiration date. As per request they do not indicate composition of contents.

Boxes carry the following label:

1. **EXPIRATION**

Product expiration date: 29/5/2012

1. **PREPARATION**

Date: 29/5/2009

Reference: 820055964

Approval: Prepared using the standards for preparation of powders for single-dose oral use. Passed quality control and marked as ‘approved’.

1. **INDICATION**

The product was requested by the Mútua de Terrassa Pharmacy Service for clinical trial EL-DSG/01/01: gluten/maltodextrin.

1. **SIGNATURE**

| **Technical Director** | **Quality Guarantee Unit** |
| --- | --- |
| [name] | [name] |

**APPENDIX 3**

**Patient quality of life**

Patients will answer a total of 36 questions (elements) concerning the effect of the illness on their quality of life (QOL). Each element is scored on a scale of 5 points, from 1 (poor QOL) to 5 (good QOL). The overall possible score on this GIQLI will therefore range from 0 to 180.

In order to facilitate interpretation, the total for the responses for each scale (symptoms, physical well-being, emotional well-being, and social relations), divided by the number of questions on each scale, will yield the score for the scale. The overall GIQLI score is the sum of the scores for all the scales.

The questions and their pertinence to each of the four scales are as follows:

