**8. How often during the past 2 weeks have you found eating to be a pleasure?**

***1.*** *All of the time* ***2****. Most of the time* ***3****. Some of the time* ***4****. Almost never* ***5****. Never*

*(Symptoms)*

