**13. How often during the past 2 weeks have you been happy with life in general?**

***1.*** *All of the time* **2.** *Most of the time* **3.** *Some of the time* **4.** *Almost never* **5.** *Never*

*(Emotional)*

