**22. During the past 2 weeks, how much have you been troubled by the medical treatment of your illness?**

***1.*** *Very much* **2.** *Much* **3.** *Somewhat* **4.** *A little* **5.** *Not at all*

*(Medical treatment)*

**23. During the past 2 weeks, how often have you been able to complete your normal daily activities (school, work, household)?**

***1.*** *All of the time* **2.** *Most of the time* **3.** *Some of the time* **4.** *Almost never* **5.** *Never*

*(Social)*

**24. During the past 2 weeks, how often have you been able to take part in your usual patterns of leisure or recreational activities?**

***1.*** *All of the time* **2.** *Most of the time* **3.** *Some of the time* **4.** *Almost never* **5.** *Never*

*(Social)*

**25. To what extent have your personal relations with people close to you (family or friends) worsened because of your illness?**

1. *Very much* **2.** *Much* **3.** *Somewhat* **4.** *A little* **5.** *Not at all*

*(Social)*

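### Appendix 3 contradicts itself on GIQLI scoring: four items are keyed against the stated direction, the 0 to 180 range fits neither scoring rule, and item 22 lies outside the four scales

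*Protocol*

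**What the plan says.** Section 8.1 lists quality of life by the GIQLI among the secondary efficacy variables. Section 8.3 has it measured at the first visit and at the last visit or early withdrawal. The scoring is in Appendix 3, which makes these statements:

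- **Direction.** For all 36 items: "Each element is scored on a scale of 5 points, from 1 (poor QOL) to 5 (good QOL".
- **Range.** "The overall possible score on this GIQLI will therefore range from 0 to 180".
- **Scale scores.** For each of four named scales (symptoms, physical, emotional, social), the responses are totalled and the total is "divided by the number of questions on each scale, will yield the score for the scale". A scale score is therefore an item mean.
- **Overall score.** "The overall GIQLI score is the sum of the scores for all the scales".

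The questionnaire follows, with a scale label under each item. Item 8 asks "How often during the past 2 weeks have you found eating to be a pleasure", item 13 "How often during the past 2 weeks have you been happy with life in general", and item 23 "how often have you been able to complete your normal daily activities"; item 24 asks the same about leisure. All four print option 1 as all of the time and option 5 as never. Item 22 is labelled as medical treatment, which is not one of the four named scales. The protocol states no recoding of any item.

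**The concern.** There are three separate conflicts within one appendix.

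1. On items 8, 13, 23 and 24 the favourable answer carries the number 1, whereas the general rule says that 1 is poor. An analyst who totals the responses by their printed numbers has four items moving against the other 32.
2. The stated range implies a sum over items, but the stated overall score is a sum of scale means. These are different scores with different weights: under the second, the 4 social items count as much as the 19 symptom items. The range given matches neither.
3. Under the sum of scale means, it is not stated whether item 22 counts.

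At stake is a listed efficacy variable in a trial of 10 patients per arm. Several different overall scores could each be defended from the same text, and one of them would dilute a real deterioration on gluten.

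**Working it through.** **Inputs, all from Appendix 3.** Items by printed label: symptoms 19 (items 1–9 and 27–36), emotional 5 (10–14), physical 7 (15–21), medical treatment 1 (22), social 4 (23–26). Check: 19 + 5 + 7 + 1 + 4 = 36. Each item is scored 1 to 5.

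**Step 1: try to reproduce 0 to 180.**

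| Rule | Minimum | Maximum |
| --- | --- | --- |
| Sum of 36 items scored 1–5 | 36 × 1 = 36 | 36 × 5 = 180 |
| Sum of 35 items (without item 22) | 35 | 175 |
| Sum of 36 items scored 0–4 | 0 | 36 × 4 = 144 |
| Sum of four scale means | 4 × 1 = 4 | 4 × 5 = 20 |
| Sum of five scale means (item 22 as a fifth) | 5 | 25 |

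No rule gives 0 to 180. The upper limit belongs to the item sum scored 1–5, where 0 cannot occur. The overall score that the appendix defines cannot exceed 20 or 25.

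**Step 2: count the reversed items.** Five items are positively worded with a good-to-poor reading: 8, 10, 13, 23 and 24. Item 10 (coping with stress) prints 1 as very poorly and 5 as very well, which agrees with the general rule. The other four do not. By scale: one reversed item in symptoms, one in emotional, two in social, none in physical or medical treatment.

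**Step 3: effect on the item sum if the printed numbers are the scores.** Take a patient with the best state on every item, and one with the worst.

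- Best: 32 × 5 + 4 × 1 = 164, not 180.
- Worst: 32 × 1 + 4 × 5 = 52, not 36.
- Span: 164 − 52 = 112, against 180 − 36 = 144. Loss: 32/144 = 22%.

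**Step 4: effect on the scale means, same assumption.**

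| Scale | Best | Worst | Span (4 if keyed as stated) |
| --- | --- | --- | --- |
| Symptoms | (18 × 5 + 1)/19 = 4.79 | (18 × 1 + 5)/19 = 1.21 | 3.58 |
| Emotional | (4 × 5 + 1)/5 = 4.2 | (4 × 1 + 5)/5 = 1.8 | 2.4 |
| Physical | 5 | 1 | 4 |
| Social | (1 + 1 + 5 + 5)/4 = 3.0 | (5 + 5 + 1 + 1)/4 = 3.0 | 0 |
| Sum of four | 16.99 | 7.01 | 9.98 |

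Against a span of 20 − 4 = 16, the loss is (16 − 9.98)/16 = 38%.

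**Step 5: the social scale.** At a uniform level q on all four social items, the printed mean is [2(6 − q) + 2q]/4 = 12/4 = 3.0 for any q from 1 to 5. The cancellation needs uniform change. If items 23 and 24 each worsen by one point while 25 and 26 stay put, the printed mean moves by 2/4 = 0.5, and upwards, as if the patient had improved.

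**Step 6: with the four items scored as 6 minus the response.** The item sum runs from 36 to 180, every scale mean from 1 to 5, and the sum of scale means from 4 to 20 (or 5 to 25).

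**The case against.** The strongest reply is that the general rule already settles the direction. If every element runs from poor at 1 to good at 5, the favourable answer to item 8 must score 5, and the printed option numbers are only labels. On that reading the totals of 164 and 52 and the flat social mean never arise. The GIQLI is cited in Section 8.3 as a validated instrument with a published translation, and a statistical analysis plan that is not shown may give the key.

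This stands to the extent that a reader might infer the quality-of-life results will be mis-scored, and the document does not show that. It shows a conflict between a rule and a form. The conflict itself remains: the instruction is to total the responses, no recoding is stated, and item 10 shows the form building direction into its numbers. The numerals are printed on all four items, so this is not a fault of text extraction. Granting recoding also does nothing for the range, the two rival overall scores or item 22.

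Further limits are fair. The lower bound of 0 enters no test, so taken alone it is a slip. The 22% is not the loss in the between-arm contrast in general: it belongs to the item sum under uniform change, while the symptom scale alone loses 0.42/4 = 10.5%. It would also go too far to say that the social scale can never move, as Step 5 shows. Equal weighting of scales is a legitimate choice, so the item sum cannot be called the right score from this document. Section 13 labels all evaluations exploratory, and any keying error would apply to both arms alike.

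**Conclusion.** The contradiction is real and can be checked by hand. Appendix 3 gives a direction that four of its own items break, a range that no stated rule produces, and four scales for a form that carries five labels.

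The losses of 22% (item sum) and 38% (sum of four scale means), and the social mean fixed at 3.0, are conditional on two assumptions: that the printed numbers are used as scores, and that all items move together. They are illustrations of what the text permits, not estimates of what will happen in the trial.

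A reader might take this as a threat to the trial's main result. The documents do not support that: the GIQLI is one of several secondary variables, clinical response is measured on separate visual analogue scales, and the sample size rests on the recurrence rate. The point should be fixed, but it is not critical.

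**What to change.** - Check the option order on the questionnaire that patients actually complete. Recoding a form that already has the favourable order would create the reversal it is meant to remove.
- Where the form matches Appendix 3, score items 8, 13, 23 and 24 as 6 minus the response, so that 5 is always good.
- State one overall score with its matching range: 36 to 180 for the item sum, or 4 to 20 (5 to 25 with a fifth scale) for the sum of scale means. Either will do if fixed before the data are analysed.
- State whether item 22 joins one of the four scales, forms its own, or is left out. If it is left out of an item sum, the range becomes 35 to 175.

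The cost is one paragraph of Appendix 3 and the scoring syntax. Data collection does not change, and responses already recorded item by item remain usable.

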**The Gastrointestinal Quality of Life Index (GIQLI)**

**1. How often during the past 2 weeks have you had pain in the abdomen?**

1. *All of the time* **2.** *Most of the time* **3.** *Some of the time* **4.** *Almost never* **5.** *Never*

*(Symptoms)*

**2. How often during the past 2 weeks have you had a feeling of fullness in the upper abdomen?**

*All of the time* ***2****. Most of the time* ***3****. Some of the time* ***4****. Almost never* ***5****. Never*

*(Symptoms)*

**3. How often during the past 2 weeks have you had bloating (sensation of too much gas in the abdomen)?**

***1.*** *All of the time* ***2****. Most of the time* ***3****. Some of the time* ***4****. Almost never* ***5****. Never*

*(Symptoms)*

**4. How often during the past 2 weeks have you been troubled by excessive passage of gas?**

***1.*** *All of the time* ***2****. Most of the time* ***3****. Some of the time* ***4****. Almost never* ***5****. Never*

*(Symptoms)*

**5. How often during the past 2 weeks have you been troubled by strong burping or belching?**

***1.*** *All of the time* **2.** *Most of the time* **3.** *Some of the time* **4.** *Almost never* **5.** *Never*

*(Symptoms)*

**6. How often during the past 2 weeks have you been troubled by gurgling noises from the abdomen?**

***1.*** *All of the time* ***2****. Most of the time* ***3****. Some of the time* ***4****. Almost never* ***5****. Never*

*(Symptoms)*

**7. How often during the past 2 weeks have you been troubled by frequent bowel movements?**

***1.*** *All of the time* **2.** *Most of the time* **3.** *Some of the time* **4.** *Almost never* **5.** *Never*

*(Symptoms)*

**8. How often during the past 2 weeks have you found eating to be a pleasure?**

***1.*** *All of the time* ***2****. Most of the time* ***3****. Some of the time* ***4****. Almost never* ***5****. Never*

*(Symptoms)*

**9. Because of your illness, to what extent have you restricted the kinds of food you eat in the past 2 weeks?**

***1.*** *Very much* ***2****. Much* ***3****. Somewhat* ***4****. A little* ***5****. Not at all*

*(Symptoms)*

**10. During the past 2 weeks, how well have you been able to cope with everyday stresses?**

***1.*** *Very poorly* ***2****. Poorly* ***3****. Moderately* ***4****. Well* ***5****. Very well*

*(Emotional)*

**11. How often during the past 2 weeks have you felt sad or depressed?**

***1.*** *All of the time* **2.** *Most of the time* **3.** *Some of the time* **4.** *Almost never* **5.** *Never*

*(Emotional)*

**12. How often during the past 2 weeks have you been nervous or anxious about your illness?**

***1****. All of the time* **2.** *Most of the time* **3.** *Some of the time* **4.** *Almost never* **5.** *Never*

*(Emotional)*

**13. How often during the past 2 weeks have you been happy with life in general?**

***1.*** *All of the time* **2.** *Most of the time* **3.** *Some of the time* **4.** *Almost never* **5.** *Never*

*(Emotional)*

**14. How often during the past 2 weeks have you felt frustrated?**

***1****. All of the time* **2.** *Most of the time* **3.** *Some of the time* **4.** *Almost never* **5.** *Never*

*(Emotional)*

**15. During the past 2 weeks have you been tired or fatigued?**

***1.*** *All of the time* **2.** *Most of the time* **3.** *Some of the time* **4.** *Almost never* **5.** *Never*

*(Physical)*

**16. During the past 2 weeks have you felt unwell?**

***1.*** *All of the time* **2.** *Most of the time* **3.** *Some of the time* **4.** *Almost never* **5.** *Never*

*(Physical)*

**17. Over the past week, have you woken up in the night?**

1. *Every night* **2.** *5 or 6 nights* **3.** *3 or 4 nights* **4.** *1 or 2 nights* **5.** *Never*

*(Physical)*

**18. Since becoming ill, have you been troubled by changes in your appearance?**

1. *A great deal* **2.** *Moderately* **3.** *Somewhat* **4.** *A little bit* **5.** *Not at all*

*(Physical)*

**19. Because of your illness, how much physical strength have you lost?**

***1.*** *A great deal* **2.** *Moderately* **3.** *Somewhat* **4.** *A little bit* **5.** *Not at all*

*(Physical)*

**20. Because of your illness, to what extent have you lost your endurance?**

***1.*** *A great deal* **2.** *Moderately* **3.** *Somewhat* **4.** *A Little bit* **5.** *Not at all*

*(Physical)*

**21. Because of your illness, to what extent do you feel less fit?**

***1****. A great deal* **2.** *Moderately* **3.** *Somewhat* **4.** *A little bit* **5.** *Not at all*

*(Physical)*

**22. During the past 2 weeks, how much have you been troubled by the medical treatment of your illness?**

***1.*** *Very much* **2.** *Much* **3.** *Somewhat* **4.** *A little* **5.** *Not at all*

*(Medical treatment)*

**23. During the past 2 weeks, how often have you been able to complete your normal daily activities (school, work, household)?**

***1.*** *All of the time* **2.** *Most of the time* **3.** *Some of the time* **4.** *Almost never* **5.** *Never*

*(Social)*

**24. During the past 2 weeks, how often have you been able to take part in your usual patterns of leisure or recreational activities?**

***1.*** *All of the time* **2.** *Most of the time* **3.** *Some of the time* **4.** *Almost never* **5.** *Never*

*(Social)*

**25. To what extent have your personal relations with people close to you (family or friends) worsened because of your illness?**

1. *Very much* **2.** *Much* **3.** *Somewhat* **4.** *A little* **5.** *Not at all*

*(Social)*

**26. To what extent has your sexual life been impaired because of your illness?**

1. *Very much* **2.** *Much* **3.** *Somewhat* **4.** *A little* **5.** *Not at all*

*(Social)*

**27. How often during the past 2 week, have you been troubled by fluid or food coming up into your mouth (regurgitation)?**

***1.*** *All of the time* **2.** *Most of the time* **3.** *Some of the time* **4.** *Almost never* **5.** *Never*

*(Symptoms)*

**28. How often during the past 2 weeks have you felt uncomfortable because of your slow speed of eating?**

***1****. All of the time* **2.** *Most of the time* **3.** *Some of the time* **4.** *Almost never* **5.** *Never*

*(Symptoms)*

**29. During the past 2 weeks have you had trouble swallowing your food?**

***1.*** *All of the time* **2.** *Most of the time* **3.** *Some of the time* **4.** *Almost never* **5.** *Never*

*(Symptoms)*

**30. During the past 2 weeks have you been troubled by urgent bowel movements?**

***1****. All of the time* **2.** *Most of the time* **3.** *Some of the time* **4.** *Almost never* **5.** *Never*

*(Symptoms)*

**31. During the past 2 weeks have you been troubled by diarrhea?**

***1.*** *All of the time* **2.** *Most of the time* **3.** *Some of the time* **4.** *Almost never* **5.** *Never*

*(Symptoms)*

**32. During the past 2 weeks have you been troubled by constipation?**

***1.*** *All of the time* **2.** *Most of the time* **3.** *Some of the time* **4.** *Almost never* **5.** *Never*

*(Symptoms)*

**33. During the past 2 weeks have you been troubled by nausea?**

***1.*** *All of the time* **2.** *Most of the time* **3.** *Some of the time* **4.** *Almost never* **5.** *Never*

*(Symptoms)*

**34. During the past 2 weeks have you been troubled by blood in the stool?**

***1.*** *All of the time* **2.** *Most of the time* **3.** *Some of the time* **4.** *Almost never* **5.** *Never*

*(Symptoms)*

**35. During the past 2 weeks have you been troubled by heartburn?**

***1****. All of the time* **2.** *Most of the time* **3.** *Some of the time* **4.** *Almost never* **5.** *Never*

*(Symptoms)*

**36. During the past 2 weeks have you had trouble controlling bowel movements?**

***1.*** *All of the time* **2.** *Most of the time* **3.** *Some of the time* **4.** *Almost never* **5.** *Never*

*(Symptoms)*

**APPENDIX 4**

**Three-day diet log**

**Instructions**

- You will use this questionnaire to record everything that you eat and drink over a three-day period, including holidays.
- It is very important that you don’t change your normal eating habits.
- To make sure that you don’t forget a meal, it is best to write down what you have consumed right after eating or drinking. Don’t forget to include all the ingredients used in each dish.
- You should also include all meals that you have away from home.
- The questionnaire has two sheets for each day. On the first you should record the dishes that you have and how they were cooked, and then on the second the ingredients and their quantities (in weight or in household measurements: tablespoon, teaspoon, cup, bowl, etc.). Try to estimate the amount of oil in tablespoons or teaspoons.
- Indicate whether the weight of foods is before or after cooking, and with or without inedible parts.
- On each sheet indicate the date and the day of the week.
- At the bottom of the page record the recipes for more complex dishes.
- Don’t forget to include sugar, bread, oil, snacks, soft drinks, alcoholic beverages, sweets, chocolate, nuts, potato chips, and so on.
- When describing food, make sure to indicate the quality and type. For milk, indicate whether it is whole, semi-skimmed, or skimmed. For meat and fish, which variety. For bread, whether it is white or whole. And also include butter and margarine where appropriate.
- If you know the brand name, include it.
- If it is a commercial product, note whether it says ‘gluten-free’ on the packaging.
- Note the type and brand of oil used, if possible.
- Indicate whether the dish was pre-cooked or prepared before eating.
- Finally, make a note of any questions or uncertainties that may arise.

**MEALS DAY ONE**

Name: Code:

Date: Age: Sex:

Day of the week: Hospital (initials):

| Time:  Place: | BREAKFAST |
| --- | --- |
| Time:  Place: | MORNING SNACK |
| Time:  Place: | LUNCH |
| Time:  Place: | AFTERNOON SNACK |
| Time:  Place: | DINNER |
| Time:  Place: | OTHER |

**DAY ONE: INGREDIENTS AND QUANTITIES**

| **FOOD ITEM (BRAND, IF KNOWN)** | **QUANTITY** | **LABELLED ‘GLUTEN-FREE’?** |
| --- | --- | --- |
|  |  |  |
|  |  |  |
|  |  |  |
|  |  |  |
|  |  |  |
|  |  |  |
|  |  |  |
|  |  |  |
|  |  |  |
|  |  |  |
|  |  |  |
|  |  |  |
|  |  |  |
|  |  |  |
|  |  |  |
|  |  |  |
|  |  |  |
|  |  |  |
|  |  |  |
|  |  |  |
|  |  |  |
|  |  |  |
|  |  |  |
|  |  |  |
|  |  |  |
|  |  |  |
|  |  |  |
|  |  |  |
|  |  |  |
|  |  |  |
|  |  |  |
|  |  |  |
|  |  |  |
|  |  |  |
|  |  |  |
|  |  |  |
|  |  |  |
|  |  |  |
|  |  |  |
|  |  |  |
|  |  |  |
|  |  |  |
| **FOOD ITEM (BRAND, IF KNOWN)** | **QUANTITY** | **LABELLED ‘GLUTEN-FREE’?** |
|  |  |  |
|  |  |  |
|  |  |  |
|  |  |  |
|  |  |  |
|  |  |  |
|  |  |  |
|  |  |  |
|  |  |  |
|  |  |  |
|  |  |  |
|  |  |  |
|  |  |  |
|  |  |  |
|  |  |  |
|  |  |  |
|  |  |  |
|  |  |  |
|  |  |  |
|  |  |  |
|  |  |  |
|  |  |  |
|  |  |  |
|  |  |  |
|  |  |  |
|  |  |  |
|  |  |  |
|  |  |  |
|  |  |  |
|  |  |  |
|  |  |  |
|  |  |  |
|  |  |  |
|  |  |  |
|  |  |  |
|  |  |  |
|  |  |  |
|  |  |  |
|  |  |  |
|  |  |  |
|  |  |  |
|  |  |  |
|  |  |  |
|  |  |  |

**MEALS DAY TWO**

Date:

Day of the week:

| Time:  Place: | BREAKFAST |
| --- | --- |
| Time:  Place: | MORNING SNACK |
| Time:  Place: | LUNCH |
| Time:  Place: | AFTERNOON SNACK |
| Time:  Place: | DINNER |
| Time:  Place: | OTHER |

**DAY TWO: INGREDIENTS AND QUANTITIES**

| **FOOD ITEM (BRAND, IF KNOWN)** | **QUANTITY** | **LABELLED ‘GLUTEN-FREE’?** |
| --- | --- | --- |
|  |  |  |
|  |  |  |
|  |  |  |
|  |  |  |
|  |  |  |
|  |  |  |
|  |  |  |
|  |  |  |
|  |  |  |
|  |  |  |
|  |  |  |
|  |  |  |
|  |  |  |
|  |  |  |
|  |  |  |
|  |  |  |
|  |  |  |
|  |  |  |
|  |  |  |
|  |  |  |
|  |  |  |
|  |  |  |
|  |  |  |
|  |  |  |
|  |  |  |
|  |  |  |
|  |  |  |
|  |  |  |
|  |  |  |
|  |  |  |
|  |  |  |
|  |  |  |
|  |  |  |
|  |  |  |
|  |  |  |
|  |  |  |
|  |  |  |
|  |  |  |
|  |  |  |
|  |  |  |
|  |  |  |
|  |  |  |
| **FOOD ITEM (BRAND, IF KNOWN)** | **QUANTITY** | **LABELLED ‘GLUTEN-FREE’?** |
|  |  |  |
|  |  |  |
|  |  |  |
|  |  |  |
|  |  |  |
|  |  |  |
|  |  |  |
|  |  |  |
|  |  |  |
|  |  |  |
|  |  |  |
|  |  |  |
|  |  |  |
|  |  |  |
|  |  |  |
|  |  |  |
|  |  |  |
|  |  |  |
|  |  |  |
|  |  |  |
|  |  |  |
|  |  |  |
|  |  |  |
|  |  |  |
|  |  |  |
|  |  |  |
|  |  |  |
|  |  |  |
|  |  |  |
|  |  |  |
|  |  |  |
|  |  |  |
|  |  |  |
|  |  |  |
|  |  |  |
|  |  |  |
|  |  |  |
|  |  |  |
|  |  |  |
|  |  |  |
|  |  |  |
|  |  |  |
|  |  |  |

